**SOURCE OF DATA**

From biopsies: Protein levels measured by Western blot and mRNA levels by PCR, fiber typing and activation of satellite cells measured by immunohistochemistry, fat cell size and activity assays for LPL.

From blood samples: Epo, total, free and bioactive IGF-I, IGFBP-1, glucose, insulin, c-peptide, free fatty acids, adiponectin, metabolites, glucagon, cortisol, catecholamines, albumin, enrichment of phenylalanine, glucose specific activity, glycerol, lactate, ALT, alkaline phosphatase, bilirubin, pro-thrombin index, carbamide, VLDL, triglyceride, VLDL-TG, proteomics analyses.

**QUALITY CONTROL AND QUALITY ASSURANCE**

The investigator and the research ethics committee or equivalent authority have access to verify all relevant data. The investigations follow GCP principles (Good Clinical Practice).

**ETHICAL CONSIDERATIONS**

**General**

It is hereby stated that the experiment will be conducted in accordance with the protocol and regulatory requirements. Information about participants is protected under the “Act on Processing of Personal Data” and the “Health Act”. Approval from the Ethics Committee of Central Region Denmark is required before the study is started. The study will be notified to the Danish Data Inspectorate, Clinical Trails Gov and if necessary to the Medicines Agency. The study will be conducted in accordance with the Helsinki Declaration II.

**Guidelines for written and oral information**

The oral and written information is provided in accordance with the Research Agency’s "Guidance on informing and obtaining consent from human subjects enrolled in biomedical research".

Potential volunteers may contact the investigator, and an appointment for oral information will be arranged. The subjects will receive the written information in advance of this meeting. The subjects will be informed about the possibility to have an accompanying person with them when the information is given. The oral information will be given by M.Sc. (Human Biology) [name] or doctor [name]. The oral Information will be given in privacy.

There will be time to ask questions, to renounce knowledge about their own health and the pamphlet "Your rights as a subject in a biomedical research project" published by the Central Research Ethics Committee will be extradited. It will be emphasized that participation is voluntary and that participation may therefore be withdrawn at any time without affecting the doctor- patient relationship.

After the oral information is given, there will be at least 1 day of reflection before obtaining the written consent.

**Foreseeable risks and inconveniences**

Placement of the intravascular catheters is associated with mild pain, and there is a low risk of infection and hematoma at the injection site. Ordinary sterile techniques will be used.

The total blood loss at each of the experimental days is approximately 320 ml. There is 10 weeks between each of the experimental days, thus, blood loss is not expected to induce symptoms. For comparison, an ordinary blood donation is approximately 500 ml.

Biopsies are associated with some discomfort, but the procedure takes place under local anesthesia. All methods have been implemented in our experimental laboratory for a long time and it is judged to be absolutely acceptable in relation to the overall objective.

The total radiation dose the participants will receive is 1.2 mSv on each of the experimental days, which represents the same dose as received when having an X-ray of the pelvis. This radiation dose results in a 0.012% increased risk for contracting a cancer disease during one's lifetime.

DEXA scanning is not associated with either pain or discomfort, but the participants receives a radiation dose of 0.1 mSv per scan equivalent to 1/30 of the annual background radiation in Denmark and 1/10 of the radiation dose received when obtaining an X-ray of the lungs.

The total radiation dose (tracer + DEXA) increases the long-term risk of cancer with a total of 0.014%. The lifetime risk of cancer after participating in the study will rise from approx. 25% to approx. 25,014 %.

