• **Biopsies:** Biopsies are taken one hour after the start of the metabolic profile and 30 minutes into the hyperinsulineamic clamp. *Fat Biopsies:* Subcutaneous fat is aspirated from the abdomen with a liposuction needle under local anesthesia and some of it is immediately frozen in liquid nitrogen. The remaining fat cells are purified by collagenase and stained with methylene blue for visualization of nukleii and cell membrane. Fat cell size is determined with a microscope and a camera is used to take pictures. *Muscle Biopsies:* A muscle biopsy is taken from the vastus lateralis with a Bergström needle. After 10-15 min. of local anesthesia (1% lidocaine), incision is made through skin and muscle fascia app. 15-20 cm above the knee. Muscle tissue is obtained and immediately frozen in liquid nitrogen or embedded in Tissue Tek and frozen. *Analyses:* Western Blot, PCR, immunohistochemical analysis, and intramuscular TG and glycogen.

• **Blood tests:** Blood samples are obtained every 20 minutes during the metabolic day. Total blood loss is around 320 ml. *Analysis:* Epo, total, free and bioactive IGF-I, IGFBP-1, glucose, insulin, C-peptide, free fatty acids, adiponectin, VLDL-TG, metabolites, glucagon, cortisol, catecholamines, albumin, phenylalanine enrichment, glucose specific activity, glycerol, lactate, ALT, alkaline phosphatase, bilirubin, pro-thrombin index, carbamid, ghrelin, and proteomics

• **VLDL studies:** These studies will be conducted before and after the 10 weeks intervention. 1 week in advance 60 ml of venous blood is sampled under sterile conditions. VLDL-TG will be insulated by ultracentrifugation (40000 g for 18 hours at 10 °C) and subsequent labeled with 20 μCi [1-^14^C] triolein. Sterility will be secured with cultivation before the sample is used for reinfusion. On the study day, the patient's own ex-vivo labeled VLDL-TG will be infused (autologous infusion) until steady state (4 hours). Blood samples will be obtained every 10 min over the last 30 min for determination of VLDL-TG SA and concentration.

• **VLDL-TG oxidation:** These studies will be performed before and after the 10 weeks intervention. VLDL-TG oxidation is measured by collecting expired air with hyamin-trapping for analysis of ^14^CO_2_, this is measured before the start of the metabolic day and 3 times during the last half an hour of the basal period.

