**Radiation:**

The long-term risks by participating is related to radiation, and can be decomposed as follows: For measurement of glucose turnover radioactive labeled glucose will be infused corresponding to a total of 0.2 mSv and for the determination of FFA turnover the radiation will be 0.4 mSv for the palmitate tracer on each of the experimental days. The infused isotopes for measurement of urea and amino acid metabolism are stable and do not constitute any risk for the participant.

The total amount of radiation the subjects are exposed to on the experimental days is approximately 1.2 mSv., which is somewhat smaller than the radiation they will normally receive during a year (the background radiation is approximately 3 mSv/year) and less than the maximal dose limit (20 mSv per year for workers over 18 years). The DEXA scan is not associated with either pain or discomfort, but is associated with a radiation dose of 0.1 mSv. per scan, which corresponds to 1/30 of the annual background radiation in Denmark and 1/10 of the radiation dose a person would receive from an x-ray of the lungs. One can theoretically calculate the total additional risk of radiation to a 0.014% increase cancer risk during one's lifetime. An average Dane will therefore increase his risk from 25.000% to 25.014%.

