**Radiation:**

The total radiation exposure is approx. 1.4 mSv., which is somewhat smaller than the radiation a person would normally receive during a year (Background radiation is approx. 3 mSv/year) and less than the dose limit (20 mSv per year for workers over 18 years). One can theoretically calculate the extra risk for developing cancer to 0.014% during one's lifetime. An average Dane will therefore increase his risk from 25.000% to 25.014%.

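### The stated radiation total (1.4 mSv, 0.014% lifetime cancer risk) omits the infused 14C-labelled VLDL, and one sentence on the daily dose conflicts with the protocol's own component sum

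*Protocol*

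**What the plan says.** All references are to the protocol.

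- **Safety, Radiation** itemises the sources. For glucose: "For measurement of glucose turnover radioactive labeled glucose will be infused corresponding to a total of 0.2 mSv". For FFA turnover: "0.4 mSv for the palmitate tracer on each of the experimental days". The urea and amino acid isotopes are described as stable and without risk. A DEXA scan "is associated with a radiation dose of 0.1 mSv. per scan". The tracer sum is given as "The total amount of radiation the subjects are exposed to on the experimental days is approximately 1.2 mSv", and the lifetime risk with DEXA as 0.014%.
- **Ethical considerations, Foreseeable risks and inconveniences** says "The total radiation dose the participants will receive is 1.2 mSv on each of the experimental days", likens this to a pelvic X-ray, and adds "This radiation dose results in a 0.012% increased risk for contracting a cancer disease during one's lifetime". It then gives 0.014% for tracers and DEXA together.
- **Layman description, Radiation** says "The total radiation exposure is approx. 1.4 mSv", with 0.014%. Its Foreseeable risks section repeats 1.4 mSv for the whole experiment, but calls this less than a pelvic X-ray.
- **Methods, Metabolic profile, VLDL studies** has VLDL-TG isolated from the participant's blood and labelled with 20 microcurie of [1-14C] triolein. The participant's "own ex-vivo labeled VLDL-TG will be infused (autologous infusion) until steady state (4 hours". Expired 14CO2 is collected afterwards.
- **Number of VLDL studies.** Methods places them both before and after the intervention, with 60 ml of blood taken a week ahead. The Safety section and its layman counterpart mention a single 60 ml labelling draw, one week before the last experimental day.

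**The concern.** The Radiation section sets out to break the long-term risk down by source. A radioactive tracer that is infused under Methods appears neither among the radioactive items nor among the stable ones. If the listed items already use up the stated total, the 14C dose cannot be inside it.

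The daily-dose sentence raises a second question. Two sections attach 1.2 mSv to different periods, yet they share one risk figure.

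The subjects are healthy volunteers, and the protocol names radiation as the source of long-term risk. Apart from their own test results and, for the training groups, a supervised programme, it expects no immediate benefit to them. An ethics committee weighing that balance needs a complete list of sources and a single dose.

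**Working it through.** **Inputs, all from the protocol**

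- Glucose tracer 0.2 mSv; palmitate tracer 0.4 mSv per experimental day (Safety, Radiation).
- Experimental days: 2 (Compensation; layman description, Metabolic profile).
- DEXA: 0.1 mSv per scan (Safety, Radiation); 2 scans, before treatment and at its end (Methods, DEXA scan).
- Risk slope: 0.012% / 1.2 mSv = 0.01% per mSv (Foreseeable risks and inconveniences).

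**Step 1. Reproduce the stated totals**

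- Per day: 0.2 + 0.4 = 0.6 mSv.
- Two days: 2 × 0.6 = 1.2 mSv; risk 1.2 × 0.01% = 0.012%.
- With DEXA: 1.2 + 2 × 0.1 = 1.4 mSv; risk 1.4 × 0.01% = 0.014%.

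Both totals and both risks match. The remainder for any other source is 1.4 − 1.4 = 0 mSv, so the total contains nothing for 14C.

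**Step 2. Take the daily-dose sentence literally**

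- Tracers: 2 × 1.2 = 2.4 mSv. With DEXA: 2.4 + 0.2 = 2.6 mSv. Risk: 2.6 × 0.01% = 0.026%.
- Against the component sum, tracers are too high by 2.4 / 1.2 = 2.0. Against the stated total, the ratio is 2.6 / 1.4 = 1.86.

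This contradicts Safety, Radiation, the layman description, and the 0.014% in the same section.

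**Step 3. Try other readings**

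- *Glucose 0.2 mSv counted once for the study:* tracers 0.2 + 2 × 0.4 = 1.0 mSv, not 1.2.
- *The extra 1.2 − 0.6 = 0.6 mSv per day is 14C:* the total is again 2.6 mSv and 0.026%, which no section states.

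Neither reading restores agreement.

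**Step 4. Illustrate the omission (assumption, not an estimate)**

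The protocol gives no mSv value for 14C. Purely for scale, apply the dose per microcurie implied by its two 3H tracers to 20 microcurie, assumed fully infused.

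- Glucose activity: 20 + 0.20 × 360 min = 92 microcurie; 0.2 / 92 = 0.0022 mSv per microcurie.
- Palmitate activity: 2 × 60 min × 0.3 = 36 microcurie; 0.4 / 36 = 0.0111 mSv per microcurie.
- For 20 microcurie: 0.04 to 0.22 mSv per infusion.

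| Infusions | Total, mSv | Lifetime risk |
|---|---|---|
| 1 | 1.44 to 1.62 | 0.0144% to 0.0162% |
| 2 | 1.49 to 1.84 | 0.0149% to 0.0184% |

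14C is a different nuclide from 3H, so the true figure may lie outside this range.

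**The case against.** The best case for the protocol is that its exposure estimate is coherent apart from one word. Safety, Radiation, both layman sections and the two risk figures in Foreseeable risks and inconveniences all agree with the component sum. Only *each* is out of line, and it errs towards overstating exposure. The doses are also small: even if 0.5 mSv per infusion is assumed, twice, the total is 1.4 + 2 × 0.5 = 2.4 mSv (0.024%), still under the 3 mSv annual background that the protocol cites. All of this stands. It limits the weight of the wording conflict and the likely harm, but it does not put 14C into the total.

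Four stronger inferences are tempting and are not supported:

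- **That the exposure figures are wrong by a factor of two throughout.** The factor is confined to one sentence. The layman figure of 1.4 mSv agrees with the listed sources and falls short only through the missing tracer.
- **That participants consented on a wrong figure.** The consent pages are not available for review. Only the layman description can be seen, and the daily-dose wording does not occur there.
- **That 14C is infused on both days.** Methods says so, but the single labelling draw in the Safety section and the layman description suggests one. The documents leave this open.
- **That the understatement has a known size.** The labelling activity is given, but neither the activity actually infused nor its dose.

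One might also place 14C in the 0.2 mSv left over when glucose is counted once (1.2 − 1.0). Nothing in the text assigns it there, and the tracer would still be unnamed.

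**Conclusion.** The point holds on two counts of unequal weight.

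1. **Omitted tracer (the main point).** The listed sources account for all of the 1.4 mSv, so the total and the 0.014% are too low by the 14C dose. That the tracer is missing is certain. How much it adds cannot be computed from the protocol, and the figures in the table are for scale only.
2. **Daily-dose sentence (minor).** It is twice the component sum and conflicts with the risk figure in its own section. This is a local wording conflict that overstates exposure.

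The conclusion on 14C rests on two experimental days, two DEXA scans, and 0.2 mSv of glucose tracer on each day. That is the reading under which the stated 1.2 and 1.4 mSv both come out exactly.

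The absolute risk is small, and nothing in randomisation, endpoints, sample size or analysis is touched. It still needs correcting, because it is a safety figure given to an ethics committee for healthy volunteers and the list of radiation sources behind it is incomplete.

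**What to change.** 1. Reconcile the number of VLDL labellings and infusions between Methods (VLDL studies), Safety, and the corresponding layman section. The total cannot be recomputed until this is settled.
2. State the 14C activity actually infused and its dose in mSv, and list it in Safety, Radiation beside glucose, palmitate and DEXA.
3. Recompute the whole-study dose and lifetime risk. With a 14C dose of x mSv per infusion and n infusions, the total is 1.4 + n·x mSv. At the protocol's own slope, the risk is 0.01% times that total.
4. Reword the daily-dose sentence in Foreseeable risks and inconveniences to agree with the components, giving each dose per day or for the study explicitly.
5. Carry one total, one risk and one X-ray comparison through both radiation sections, both sections on foreseeable risks, and any participant information based on them. At present 1.2 mSv equals a pelvic X-ray in one place and 1.4 mSv is less than one in another.

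The cost is one dosimetry figure and a text correction, with the corrected figure going to the ethics committee. The stated exposure becomes slightly less favourable. Design and analysis do not change.

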**Benefits of participation in the study**

The subjects may, upon completion of the project, get the results of own examinations and blood tests. The subjects who are randomly assigned to the training group will also engage in a 12-week supervised training regime. Besides this, it is estimated that there are no other immediate benefits for the individuals by participating in the study.

**Bio bank**

Blood and tissue samples will be used for analyses after the end of the study and possibly excess tissue will be destroyed thereafter. A bio bank is therefore not established. Blood samples will be sent to the U.S. where the proteomic analysis will be performed. Samples will be destroyed here if there is more left after the analyses are conducted. All the analyses are scheduled to be performed by the end of 2014.

**HANDLING AND ARCHIVING OF DATA**

In order to minimizing error when entering data, double entry and subsequent review will be performed. All data is stored in anonymous form. Data will be archived at the Department of Endocrinology and Internal Medicine, Aarhus University Hospital for 15 years after the study ends.

**FINANCE AND INSURANCE**

Funding: The project is funded by the Department of Endocrinology and Internal Medicine, MEA, and through a grant from the World Anti Doping Agency (WADA) (200,000 US$). Additionally, applications will be sent to private research funds. Investigator [name] is employed as a post doc at Aarhus University Hospital. The salary is paid by the Department of Endocrinology and Internal Medicine, MEA and WADA. PhD Student [name] is paid by a stipend from Aarhus University.

Participants are covered in accordance with the law on complaints and compensation in accordance with the national health care services.

**PUBLICATION**

After termination of the study several English language articles will be prepared for publication in scientific per-reviewed journals. Both positive negative results will be published.

**COMPENSATION**

Participants in the study will receive a compensation of 5500 DDK if they are allocated to the training group and 4500 DDK if part of the control group. This covers any inconvenience associated with the experiment. Transportation to and from the two experimental days will be covered but the subjects themself will pay the remaining. The compensation is taxable. If a participant is withdrawn from the study he will receive compensation in accordance to the participation time.

Layman description

**TIMETABLE**

Estimated start: June 2011

Expected completion: August 2012

**BACKGROUND**

Erythropoietin (Epo) is produced in the kidneys when the oxygen levels in the blood become too low. Epo stimulates the formation of new red blood cells in the bone marrow. Epo is used as a medicine for kidney and cancer diseases, leading to a lack of red blood cells.

Epo increases red blood cell production and hence the amount of oxygen that can be transported around the body. It is shown that prolonged use of synthetic Epo (rHuEpo) leads to an increase in the period of time a given physical work can be performed, therefore it will continue to be abused by athletes, especially in endurance sports. This happens despite the fact that rHuEpo was added to the anti-doping list already in 1990. It is therefore important to find a robust method to detect this abuse. Not only to ensure fair competition but also to reduce the abuse and the side effects that follow, e.g increased risk of blood clots.

The existing method for measuring the abuse of rHuEpo approved by the World Anti-Doping Agency (WADA) is based on differences in the sugar groups bound to rHuEpo and Epo produced in the body, respectively. Whether this approach will be effective against new synthetic Epo products are still unknown. Future Epo tests should therefore be based on biological markers, that changes when Epo levels rise. Various blood markers related to the amount of red blood cells have already been investigated, but these methods have proven to be very conservative, since the boundaries of the normal range is very wide in order to avoid false-positive results.

Proteomics is a method by which you can look at all the proteins in blood at the same time. Even proteins that have changed very little can be distinguished. The main objective of this project is to investigate the effect of prolonged treatment with rHuEpo on changes in blood proteins in healthy young men. We have in a previous study with 16 days of treatment with rHuEpo shown changes in blood proteins. It is hoped that some of these proteins can be used as marker for Epo abuse in the future. We furthermore want to explore the effect of physical activity on these proteins, since athletes will always be physically active. The effect of physical activity itself is therefore important to elucidate, if these proteins should be used in a future anti-doping test.

Epo receptors are found in many different types of tissues other than the bone marrow, for example, different cells in the brain, cancer cells, cells in the gut, and especially muscle tissue. The effects of Epo in these tissues are not fully elucidated.

We also want to investigate the effects of rHuEpo on fat and muscle tissue, and possible effects on the turnover of fat, sugar, and protein.

**PURPOSE**

To identify new biomarkers in the blood that can be used to detect rHuEpo abuse. In addition, to examine the effect of 10 weeks of training and treatment with rHuEpo at a wide range of other parameters such as turnover of fat, sugar, and protein, and changes in the muscle tissue.

**STUDY PLAN**

40 healthy young men will be included in the present study they will be recruited through the homepage www.forsøgsperson.dk and various notices on Aarhus University.

**Inclusion Criteria:**

• Written consent before study entry

• Adult, healthy men

• Age >18 years and <35 years

• Normal weight (BMI: 18-27)

• Untrained (<2 hours of physical activity per week)

• Non smoking

**Exclusion criteria:**

• Chronic disease

• Blood pressure above 135/85

• Hematocrit above 45%

**Design:**

• The subjects will be randomly allocated to one of the following 4 groups (10 persons in each group)

o Placebo treatment

o Placebo treatment + endurance training

o rHuEpo treatment

o rHuEpo treatment + endurance training

• Subjects are examined before and after 10 weeks rHuEpo/placebo treatment and again after a 3 weeks washout period.

• EPO (~50IU/kg)/placebo (saline) is administered using a small syringe under the skin twice a week for the first 3 weeks at a dosage of 2x 40μg, and once a week from week 4-12 at a dosage of 20μg.

• The endurance training will consist of 1 to 1.5 hours of cycling at 65-80% of maximum oxygen uptake, 3 times weekly.

 
[figure not shown]

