**PURPOSE**

To identify new serum biomarkers to detect abuse of rHuEpo. Secondarily, we want to examine the effects of 10 weeks of rHuEpo treatment and training on a wide range of other parameters e.g. turnover of fat, carbohydrate, and protein, muscle type changes, and activation of satellite cells in skeletal muscle.

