**DESIGN**

• The experiment is a single-blind, randomized study.

• 40 subjects in total will be included and randomly assigned to one of the following groups (n = 10);

o Placebo treatment

o Placebo treatment + endurance training

o rHuEpo treatment

o rHuEpo treatment + endurance training

• Subjects are examined before and after 10 weeks of rHuEpo/placebo treatment, and after a 3 weeks washout period.

• EPO (Darbepoietin alpha) (~50IU/kg)/placebo (saline) is administered s.c. twice a week for the first 3 weeks at a dosage of 2x40 μg, and once a week from week 4-10 at a dosage of 20 μg.

• The endurance training will consist of 1 to 1.5 hours of cycling at 65-80% of VO_2_max, 3 times weekly. This was previously shown to cause an increase in maximum oxygen uptake (Midgley et al., 2006).

[figure not shown]

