- **MRI scanning:** MRI will be used to measure intrahepatic and intramyocellular lipid content. The liver and the tibialis anterior muscle will be scanned using a technique that combines MR imaging with localized proton MR spectroscopy with a voxel of 3x3x3cm, a 1.5T MR unit will be used together with a breath holding for 17 sec. Before entering the scanning room the subject will be asked about contra induced circumstances in relation to normal procedures for MRI. The subjects will be asked to remove any metal from pockets and remove jewelry. The subjects will be informed that MRI is a safe procedure without any risk of radiation. There will be a loud sound during the scanning, and the subjects will be given earplugs.

 
[figure not shown]

**Serum:** Serum will be collected before the study and on days 8, 15, 21, 36, 50, 64, 71, and 78 and 92 during the wash-out period. Hematological levels will be measured throughout the study, and treatment will be discontinued if the values are abnormal (Hematocrit >55%). The following will be measured; Hemoglobin, erythrocytes, iron, transferrin, ferritin, reticulocytes, haptoglobin, albumin, alkaline phosphatase, bilirubin, LDH, plasma hemoglobin, VLDL, FFA, ghrelin, and cholesterol. Proteomics analysis will be performed on blood samples taken before the study at baseline and on days 21, 71, and 92.

**Blood pressure measurements:** The subjects' blood pressure will be monitored throughout the study on the days when blood will be sampled. This is done to ensure that the treatment does not induce increased blood pressure.

Blood and tissue samples are used for analyses, and thereafter destroyed. A bio bank is therefore not created.

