**Benefits of participation in the study**

The subjects may, upon completion of the project, get the results of own examinations and blood tests. The subjects who are randomly assigned to the training group will also engage in a 12-week supervised training program. Besides this, it is estimated that there are no other immediate benefits from participating in the study.

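### The protocol gives two lengths for weekly dosing and two for training, so the meaning of the day 71, 78 and 92 serum samples depends on which text is followed

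*Protocol*

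**What the plan says.** **Dosing.** The main protocol's Design section gives the maintenance phase as "and once a week from week 4-10 at a dosage of" 20 micrograms. The lay description's Design section gives it as "and once a week from week 4-12 at a dosage of" 20 micrograms. The bullet just before that lay line reads "Subjects are examined before and after 10 weeks rHuEpo/placebo treatment and again after a 3 weeks washout period", which agrees with the main Design section: "Subjects are examined before and after 10 weeks of rHuEpo/placebo treatment, and after a 3 weeks washout period".

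**Training.** The main Purpose section sets out to "examine the effects of 10 weeks of rHuEpo treatment and training", and the lay Purpose section also says 10 weeks. Under Benefits of participation in the study, the main text says that men allocated to training "will also engage in a 12-week supervised training regime", and the lay text says that they "will also engage in a 12-week supervised training program". The training bullets in both Design sections give session length, intensity and weekly frequency, but no number of weeks.

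**Sampling.** The primary endpoint is serum proteomics, measured at baseline and on days 21, 71 and 92 (main Methods, Serum paragraph; lay Methods, Blood tests). That Serum paragraph ends its list of collection days with "71, and 78 and 92 during the wash-out period". The main Safety section and the lay Blood tests paragraph place day 71 in the treatment period and days 78 and 92 in the washout.

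**The concern.** Drug and training are the two factors of the four-group design, and each is given two durations. The training conflict lies wholly within the main protocol (Purpose against Benefits), so it is not only a slip in the lay summary.

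Two of the three post-baseline proteomics samples, days 71 and 92, take their meaning from when dosing and training stop. The Background section also makes the effect of physical activity on the markers an explicit aim, so the length of training matters for interpretation as well. Finally, the participants are healthy volunteers, and the Safety section names thrombosis and hypertension as possible risks of prolonged treatment. The amount of drug given should not depend on which half of the document is read.

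**Working it through.** **Inputs.** Weekly dosing in weeks 4-10 (main Design) or weeks 4-12 (lay Design), 20 micrograms per weekly dose; 3-week washout (both Design sections); training 3 times weekly for 10 weeks (Purpose) or 12 weeks (Benefits); samples on days 71, 78 and 92.

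**Assumptions.** Day 1 is the first treatment day, so week k covers days 1 + 7(k - 1) to 7k, and W weeks are complete at day 1 + 7W. The document does not state its day numbering; starting at day 0 moves each completion day one day earlier. The dosing weekday is not stated either.

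**Reproducing the stated calendar.** 10 weeks: 1 + 70 = day 71. Three more weeks: 71 + 21 = day 92. Both days come out exactly (70 and 91 if counting from day 0).

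**Comparing the two dosing texts.**

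| Quantity | Weeks 4-10 | Weeks 4-12 |
|---|---|---|
| Last dosing week | days 64-70 | days 78-84 |
| Treatment complete (day-1 / day-0 count) | day 71 / 70 | day 85 / 84 |
| End of a 3-week washout | day 92 / 91 | day 106 / 105 |
| Day 92 minus completion | 21 / 22 days | 7 / 8 days |
| Day 92 minus last dose, if given on the first day of the week (day-1 count) | 92 - 64 = 28 days | 92 - 78 = 14 days |
| Weekly doses | 10 - 4 + 1 = 7 | 12 - 4 + 1 = 9 |
| Drug in this phase | 7 x 20 = 140 micrograms | 9 x 20 = 180 micrograms |

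Under weeks 4-12, day 71 is the first day of week 11, so the doses of weeks 11 and 12 are still to come. With a day-0 count and dosing at the start of the week, the week 11 dose would fall on day 70 and one dose would remain. Day 78 lies in dosing week 12 under either count, although it is labelled washout.

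**Training.** 3 x 10 = 30 sessions against 3 x 12 = 36. If 12 weeks of training start on day 1 (an assumption; no start day is given), the trained groups are still training on days 71 and 78 and stop about a week before day 92 (7 or 8 days). The day 92 sample in those groups would then combine drug washout with recent training. The last maximal oxygen uptake test is set for the day after the final metabolic day (main Methods), and the lay Methods place that metabolic day after 10 weeks of treatment. On the same assumption, the test would come about two weeks before a 12-week training programme ended.

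**The case against.** The strongest reply is that the intended schedule can be recovered from the document. The 12-week dosing range occurs once, in the lay description. Both Purpose sections, the main Design section, the VLDL paragraphs in Methods, the lay metabolic-profile paragraph, the spacing of experimental days and the serum calendar all fit 10 weeks. The 12-week training figure appears only under Benefits, not in Design or Methods. The design figures are not shown and may carry a schedule. All of this stands, and it means that the dosing conflict is one outlying line rather than an even split. It does not remove the contradictory sentences, and the shown Design text gives no training duration that would settle the second conflict.

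Three stronger readings are tempting, and the document does not support them:

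- *The randomised drug comparison would be biased.* Placebo follows the same injection schedule as rHuEpo in both texts, and within each training stratum rHuEpo and placebo would train for the same time. That comparison stays matched.
- *A conclusion about how long a marker stays detectable would be wrong.* The stated purpose is to identify biomarkers. No detection-window endpoint or hypothesis is given, so there is no such claim to invalidate.
- *The protocol itself calls day 71 the end of treatment.* It places day 71 within the treatment period. That day 71 marks the end of treatment is an inference from the arithmetic above.

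**Conclusion.** The contradiction is real for both interventions and should be corrected. Its effect is on what the later time points represent, not on the balance of the drug comparison. Under the one outlying dosing line, the interval from the end of the treatment period to day 92 falls from about 21-22 days to about 7-8, and each rHuEpo participant would receive two more weekly doses (40 micrograms). Under the 12-week training text, trained groups would have stopped training only about a week before the washout sample. The baseline and day 21 samples are unaffected.

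The day counts rest on the day-numbering convention, the 28- and 14-day figures on an assumed dosing weekday, and the training result on an assumed start on day 1. That the calendar fits 10 plus 3 weeks is an observation about consistency; the choice of duration belongs to the sponsor.

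**What to change.** Reconcile the following passages to one sponsor-chosen dosing length and one training length:

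- main protocol: Purpose, Design, and Benefits of participation in the study;
- lay description: Purpose, Design, Methods (metabolic profile and blood tests), and Benefits of participation in the study.

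Add the training duration to the Design training bullets, and state whether training continues after the last injection. Define the day 71, 78 and 92 samples relative to the last dose and the last training session, and record both dates for each participant. Whether results are also reported by days since last dose is an optional analysis choice.

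The cost is a text amendment to the protocol and the lay description, plus two date fields per participant.
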